### Data monitoring committee

An independent Data Monitoring Committee (DMC) has been established to address any uncertainties related to data collection and registration. The DMC is composed of a chair (an experienced anesthesiologist), a professor of statistics, a pharmacologist, and a thoracic surgeon. If any ambiguity arises in data collection or registration, DMC will discuss these issues to reach a final consensus.

Both intervention methods are routinely performed at our center, and we anticipate that serious adverse events during this study will be infrequent. Any adverse event, whether related to the study interventions or not, must be reported to the DMC within 24 h using an “Adverse Event Form.” In the event of serious adverse events, such as unexpected deterioration of patients’ clinical status post-surgery, the research team could request unmasking of allocation and adjust or discontinue the study medications. The DMC will conduct ongoing reviews to assess safety and provide recommendations regarding the suspension or termination of the study.

### Study outcomes

The primary outcome of this trial is the average numeric rating scale (NRS) pain scores at rest over 72 h postoperatively (average of three 24-h time points: 24, 48, and 72 h). Secondary outcomes include NRS pain scores at rest and during activity at 24, 48, and 72 h postoperatively; Quality of Recovery 15 scores at 24, 48, and 72 h postoperatively; time to first press on the PCIA device; total amount of opioid consumption within 72 h postoperatively, converted to morphine milliequivalents; the time to initiate independent bedside mobilization, the length of the postoperative hospital stay and incidence of chronic pain (defined as an NRS score ≥ 1) at 3 months post-surgery. Safety outcomes included postoperative adverse events and complications within 72 h, including postoperative nausea and vomiting (PONV), fever, headache, dizziness, itching, constipation, ileus, urinary retention, insomnia, new-onset atrial fibrillation, severe ventricular arrhythmia, cardiac arrest, chest tightness, pulmonary embolism, pulmonary atelectasis, chylothorax, pneumothorax, deep vein thrombosis, and organ failure. The definitions of adverse events are displayed in Supplementary Table S1.

### Sample size calculation

Between March and June 2024, we conducted a prospective study in which patients received postoperative ultrasound-guided ESPB or ICNB under thoracoscopic visualization at the end of surgery using LB, with 10 patients per group. The results showed that the average NRS pain score at rest over the 72-h after surgery was 2.88 ± 1.75. The minimal clinically important difference (MCID) in pain scores for acute postoperative pain has been defined as 1 across a variety of surgeries (20–22). The sample size calculation was performed using a two-group t-test, assuming a standard deviation of 1.75, an 80% power, and a 0.05 level of significance. Considering a 15% dropout rate, the study will enroll a total of 120 patients, with 60 in each group. The sample size calculation was conducted using PASS software (version 15, PASS Institute Inc.).

### Statistical analysis

Descriptive statistics will be used to summarize baseline characteristics and demographic data without conducting between-group comparisons. Continuous data will be reported as median with interquartile ranges (IQR) or means with standard deviations (SD), depending on data distribution. Categorical data will be displayed as counts and percentages. The independent t-test or the Mann–Whitney U test will be used to assess between-group differences in continuous data, while the Chi-squared test or Fisher’s exact test will be applied for categorical data analysis, as appropriate.

For the study outcomes, the treatment effect of study interventions will be evaluated using odds ratios for binary data and differences for continuous data, each reported with 95% confidence intervals. The primary and secondary outcomes will be further analyzed using multivariable linear regression or logistic regression, adjusting for baseline covariates (age, sex, type of surgery, and number of ports). Subgroup analyses for the average pain score will be performed according to age (<60 years old vs. ≥ 60 years old), sex (female vs. male), BMI (< 25 vs. ≥ 25), surgery type (wedge resection vs. segmentectomy vs. lobectomy), and the number of port (single or multiple). Correction for multiple testing is planned for secondary outcomes using the Benjamini-Hochberg method.

The analysis will be performed on the modified intention-to-treat population, comprising all randomized patients who undergo VATS lung resection and for whom primary outcome are available. We do not plan to conduct missing data imputation or interim analysis. A Two-sided *p-*value of <0.05 will be considered statistically significant. Statistical analyses will be performed with R statistical software (version 4.3.0, R Foundation for Statistical Computing) by independent statisticians.

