Our study has several limitations. First, we are unable to perform sensory testing to assess the effectiveness of the nerve blocks after surgery due to the intervention being conducted under general anesthesia. Second, pain assessments are conducted at three-time points during the first three postoperative days, with no additional time points evaluated beyond this period. Third, some patients are discharged within 72 h after surgery, necessitating follow-up of their NRS scores via telephone.

In conclusion, this randomized clinical trial is designed to evaluate the efficacy of anesthesiologist-performed ESPB using liposomal bupivacaine compared to surgeon-administrated ICNB with LB in VATS lung resection. We expect that LB can be safely employed in ultrasound-guided ESPB, and liposomal bupivacaine for anesthesiologist-performed ultrasound-guided ESPB will be more effective than surgeon-administrated thoracoscopic ICNB in reducing the average postoperative pain over the 72-h period.

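### For rare safety events the odds ratio, the only effect measure named for binary outcomes, will often be 0, infinite or undefined at 60 per arm; a risk difference should be added

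*Protocol article*

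**What the plan says.** In the protocol article, Statistical analysis, the effect of treatment on the study outcomes is to be "evaluated using odds ratios for binary data and differences for continuous data, each reported with 95% confidence intervals". The section names neither a risk difference nor a risk ratio.

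The Study outcomes section contains the binary outcomes to which this applies. One is a secondary outcome, the "incidence of chronic pain (defined as an NRS score ≥ 1) at 3 months post-surgery". The others are the safety events, introduced by "Safety outcomes included postoperative adverse events and complications within 72 h, including postoperative nausea and vomiting (PONV), fever, headache, dizziness, itching, constipation, ileus" and ending with "severe ventricular arrhythmia, cardiac arrest, chest tightness, pulmonary embolism, pulmonary atelectasis, chylothorax, pneumothorax, deep vein thrombosis, and organ failure". The full list has 19 separate events. Because it stands among the study outcomes, the odds-ratio sentence covers it.

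Two other statements in Statistical analysis bear on binary data. "Categorical data will be displayed as counts and percentages", and the Chi-squared "test or Fisher’s exact test will be applied for categorical data analysis, as appropriate".

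The article gives no expected rate for any safety event. The Data monitoring committee section says only that "we anticipate that serious adverse events during this study will be infrequent". On safety, the Discussion states: "We expect that LB can be safely employed in ultrasound-guided ESPB".

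**The concern.** The odds ratio needs at least one event in each arm to have a finite, non-zero estimate. With 60 patients per arm, an event such as cardiac arrest, pulmonary embolism, chylothorax or organ failure may well not occur in one arm, or in either. The planned measure then gives 0, infinity or no value.

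For a rare serious event, a trial of this size can mainly show how large an excess in either arm the data rule out. That is a statement about the difference in risk, and it can be made even when nobody has the event. The odds ratio cannot make it when both arms are empty. So the planned summary is weakest for the most serious events on the list, while the article expects to support the safety of one of the two techniques.

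**Working it through.** **Inputs.** From the article: 1:1 allocation, 60 per arm, 15% dropout, 19 safety events. Assumed: the true event rates, shown as a range, equal in both arms.

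**Sample size first.** A two-sided two-group t-test with difference 1, SD 1.75, alpha 0.05 and 80% power needs 50 per arm (power 0.808). Then 50/(1 - 0.15) = 58.8, so 59 per arm, against the stated 60. The 60 per arm is sound. After 15% dropout, 60 × 0.85 = 51 remain.

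**Chance of a zero cell.** With true risk p and n per arm, the chance that one given arm has no event is q = (1 - p)^n. At least one arm is empty with probability 1 - (1 - q)^2, and both with probability q^2. For p = 1% and n = 60, q = 0.99^60 = 0.547, so 1 - 0.453^2 = 0.795 and 0.547^2 = 0.299.

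| True risk (assumed) | At least one arm empty, n = 60 | Both empty, n = 60 | At least one arm empty, n = 51 |
|---|---|---|---|
| 0.5% | 93.3% | 54.8% | 94.9% |
| 1% | 79.5% | 29.9% | 83.9% |
| 2% | 50.7% | 8.9% | 58.6% |
| 3% | 29.6% | 2.6% | 37.8% |
| 5% | 9.0% | 0.2% | 14.1% |
| 10% | 0.4% | 0.0% | 0.9% |

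**How many of the 19 events.** The expected number is the sum of 1 - (1 - q)^2 over the events, at 60 per arm. Two sets of assumed rates were tried.

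- Lower set: one event at 0.1%, three at 0.2%, three at 0.3%, one at 2%, four at 3%, four at 5%, and one each at 10%, 15% and 25%. Expected: 8.9 events with an empty arm, 5.5 of them with both arms empty.
- Higher set: one at 0.2%, two at 0.5%, four at 1%, two at 5%, four at 10%, three at 15%, and one each at 25%, 30% and 40%. Expected: 6.2 and 3.1.

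This gives about 6 to 9 of 19, but only under these rates.

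**What the two measures report.** The exact odds-ratio interval is the conditional (Fisher-type) one. For 0 v 1, the chance that the single event falls in the second arm is 1/(1 + OR). Setting this to 0.025 gives an upper limit of 39. The Newcombe interval for the risk difference combines the Wilson limits (l, u) of the two arms:

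- lower: (p1 - p2) - √[(p1 - l1)² + (u2 - p2)²]
- upper: (p1 - p2) + √[(u1 - p1)² + (p2 - l2)²]

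For 0/60 the Wilson upper limit is 3.84/(60 + 3.84) = 6.0%, so 0 v 0 gives ±6.0 points.

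| Events, first v second arm (60 each) | Exact 95% CI, odds ratio | Newcombe 95% CI, risk difference (points) |
|---|---|---|
| 0 v 0 | 0 to infinity | -6.0 to +6.0 |
| 0 v 1 | 0 to 39.0 | -8.9 to +4.5 |
| 0 v 2 | 0 to 5.3 | -11.4 to +3.2 |
| 0 v 3 | 0 to 2.4 | -13.7 to +1.9 |
| 1 v 3 | 0.006 to 4.2 | -12.1 to +4.6 |
| 6 v 9 | 0.17 to 2.15 | -17.3 to +7.3 |
| 12 v 18 | 0.23 to 1.46 | -24.9 to +5.5 |

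The usual Wald interval cannot be computed in the first four rows, because its standard error contains 1/0. The risk difference has two finite limits in every row.

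**The case against.** A reader might infer that the safety comparison as a whole yields no usable interval. The documents do not support that. Events at about 5% or more will nearly always give an ordinary two-sided odds-ratio interval, as 6 v 9 shows. With one empty arm, the exact interval still has one informative limit, and 0 v 3 already excludes odds ratios above 2.4. Only a table with both arms empty says nothing. Nor can one say from the article that many of the 19 events are affected, because it gives no rates.

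The plan also reports counts and percentages by arm and names Fisher's exact test, so a reader who sees 0/60 in both arms can work out the limits. This stands in part: the absolute risks are not hidden. But counts and percentages are not an interval for the comparison, and a non-significant test of a rare event does not say how large an excess is excluded.

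The handling of zero cells may be set in a statistical analysis plan that is not shown, and its absence here is no fault. Adding 0.5 to each cell, for instance, gives finite limits: 0.02 to 51 for 0 v 0, and 0.013 to 8.2 for 0 v 1. Such a rule would still leave only a relative measure, with limits that depend on the added constant. The point here is the effect measure that the article does state.

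For chronic pain, one might call the odds ratio misleading because it lies further from 1 than the risk ratio. At an assumed 45% v 30% it is (0.45/0.55)/(0.30/0.70) = 1.91, against a risk ratio of 0.45/0.30 = 1.50. Crude and adjusted odds ratios can also differ under perfect balance. Both are properties of a legitimate measure, not errors, and the percentages will stand beside it.

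**Conclusion.** The point holds for rare safety events only. At a true risk of about 2% or less in both arms, an empty arm is at least as likely as not, and the planned effect measure then has no finite, non-zero value. The size rests on assumed equal rates and on 60 per arm; at 51 per arm the problem is somewhat more frequent. The primary outcome, the non-binary secondary outcomes and the commoner adverse events are unaffected. This is a reporting weakness in a stated analysis, of modest weight and cheap to remove.

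**What to change.** In Statistical analysis, add one sentence. For each safety event, the risk difference will be reported with a score-type 95% confidence interval (Newcombe or Miettinen-Nurminen, one of them named in advance), together with the exact upper 95% limit for any arm with no event. For 0/60 the upper limit of the two-sided exact interval is 1 - 0.025^(1/60) = 6.0%. Keep the odds ratio where both arms have events.

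A risk difference beside the odds ratio for chronic pain is an optional addition, not a correction.

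The change needs a few lines of R and no new data or patients. The only downside is one more column in the safety table.

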After surgery, all patients are provided with patient-controlled intravenous analgesia (PCIA), consisting of 100 μg sufentanil diluted to 100 mL with normal saline (final concentration: 1 μg/mL). The PCIA device is programmed with the following parameters: a background infusion rate of 1 mL/h, a self-controlled bolus of 2 mL, a lockout interval of 10 min, and a maximum hourly dose of 20 mL. The PCIA is initiated immediately after surgery and continues for 48 h postoperatively. If pain persists, defined as a numeric rating scale (NRS) pain score of ≥4, patients are instructed to self-administer sufentanil via PCIA. If pain remained unrelieved, intravenous rescue opioids (sufentanil, fentanyl, oxycodone, tramadol, or morphine) were permitted. Additionally, both groups will receive an initial intravenous dose of 50 mg flurbiprofen axetil at the end of surgery. This will be followed by two daily doses of 50 mg intravenous flurbiprofen axetil administered at 08:00 and 16:00 (totaling 100 mg per day) as part of the multimodal analgesia regimen on postoperative days 1 and 2.

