### Data collection and registration

Trained independent investigators who are blinded to group assignment will collect the patients’ demographic data and follow-up outcomes.

Pain intensity is assessed using the numeric rating scale (NRS, 0–10; 0 = no pain, 10 = worst possible pain) at rest and during activity at 24, 48, and 72 h postoperatively, with a 2-h time window. Quality of Recovery-15 (QoR-15) scores are recorded at the same time points to evaluate overall recovery (19). This questionnaire measures five domains: pain, psychological state, emotional state, independence, and comfort. It consists of 15 statements rated on a 0–10 scale, with total scores ranging from 0 to 150. Higher scores indicate better postoperative recovery. Additionally, the time to the first press on PCIA device and the total amount of opioid consumption through 0–72 h postoperatively are documented. The time to first press on PCIA is measured in hours, calculated as the time of the first press on PCIA minus the time of the end of surgery. Total opioid consumption is standardized by converting all opioids to intravenous morphine milligram equivalents (MMEs) for each patient. For patients discharged before 72 h, follow-up assessments are conducted via telephone. The incidence of chronic pain (defined as NRS score ≥ 1) is evaluated through phone calls at 3 months postoperatively, with a permitted time window of 3 months ±7 days. Furthermore, the time to initiate independent bedside mobilization, and the length of the postoperative hospital stay are recorded. Independent bedside mobilization is defined as the patient being able to perform activities around the bed without assistance from others. The time to initiate independent bedside mobilization is measured in hours, i.e., the time of the event minus the time of the end of surgery.

All data will be entered into electronic case report forms (eCRFs) under the oversight of trained research personnel. An electronic trial database will be generated based on these eCRFs. Once data entry is finalized, the database will be locked and de-identified. The anonymized dataset will subsequently be transferred to an independent statistician for final analysis according to the prespecified statistical plan.

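### Time to first PCIA press is right-censored when the pump stops at 48 h, but the plan assigns it methods for fully observed continuous data and gives no rule for patients who never press.

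*Protocol article*

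**What the plan says.** All places are in the Methods of the protocol article.

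- **Outcome.** Study outcomes lists time to first press as a secondary outcome. Data collection and registration defines it, counting from when surgery ends: "The time to first press on PCIA is measured in hours, calculated as the time of the first press on PCIA minus the time". It gives no value for a patient who does not press.
- **Observation period.** Study interventions states: "The PCIA is initiated immediately after surgery and continues for 48 h postoperatively". Table 1 accordingly records first press in the PACU and at 24 and 48 h, and not at 72 h.
- **Unadjusted analysis.** Statistical analysis states: "The independent t-test or the Mann–Whitney U test will be used to assess between-group differences in continuous data". Effects are to be "evaluated using odds ratios for binary data and differences for continuous data, each reported with 95% confidence intervals".
- **Adjusted analysis.** "The primary and secondary outcomes will be further analyzed using multivariable linear regression or logistic regression", with age, sex, type of surgery and number of ports as covariates.
- **Missing data.** "We do not plan to conduct missing data imputation or interim analysis".

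The article nowhere mentions censoring, Kaplan–Meier, log-rank, Cox regression or restricted mean time. Time to independent mobilization is defined in the same way, again counting from when surgery ends: "The time to initiate independent bedside mobilization is measured in hours, i.e., the time of the event minus the time". Table 1 records it at 24, 48 and 72 h.

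**The concern.** For a patient who has not pressed when the pump stops, all that is known is that the time exceeds 48 h. None of the named methods represents that. The analyst must either leave the patient out or put a number in, and the article does not say which.

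Leaving the patient out compares only those whose pain led them to press. Pressing happens after randomization and depends on how well the block works. The more effective block would contribute fewer patients, with its longest press-free times removed, so the contrast shrinks towards zero. Putting in 48 h keeps everyone, but a linear model then takes a lower bound as an observed press time.

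The two choices can give different answers on the same data, so the choice should be fixed before unblinding.

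**Working it through.** **The plan's own figure.** The article gives no number for this outcome. Its sample size for the primary outcome can be checked. A two-sample t-test with difference 1 (the stated MCID), SD 1.75, two-sided alpha 0.05 and 80% power needs 50 per arm. 50 / 0.85 = 58.8, so 59 per arm or 118 in total, close to the stated 120. This point does not affect that figure.

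**Inputs.** From the article: pump stop at 48 h, and 60 per arm with 15% dropout, so 60 × 0.85 = 51 per arm. Assumed, because the article gives nothing: exponential press times, a hazard ratio of 0.5 in favour of ESPB (the hypothesized direction), and the share p never pressing on ICNB.

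**Formulas.**
- ICNB rate: λ = −ln(p) / 48. ESPB rate: λ / 2. Share never pressing on ESPB: √p.
- For an arm with rate r and never-press share q = exp(−48r):
  - mean time among pressers = 1/r − 48q / (1 − q)
  - restricted mean to 48 h = (1 − q) / r

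**Worked case, p = 0.20.** λ = 1.609 / 48 = 0.0335, so 1/λ = 29.82 h. The ESPB mean is 59.65 h, with √0.20 = 0.447 never pressing.
- Pressers only, ICNB: 29.82 − 48 × 0.20 / 0.80 = 17.82 h.
- Pressers only, ESPB: 59.65 − 48 × 0.447 / 0.553 = 20.82 h. The difference is 3.0 h.
- Restricted mean, ICNB: 0.80 × 29.82 = 23.86 h.
- Restricted mean, ESPB: 0.553 × 59.65 = 32.97 h. The difference is 9.1 h.

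**Results.** Differences come from the formulas, power from simulation.

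| Never press, ICNB / ESPB | Difference, pressers only | Difference, restricted mean | Power, pressers only | Power, Mann–Whitney with never-pressers at 48 h | Power, log-rank |
|---|---|---|---|---|---|
| 5% / 22% | 4.7 h | 9.7 h | 40–45% | 82% | 91% |
| 20% / 45% | 3.0 h | 9.1 h | 14–15% | 77% | 81% |
| 40% / 63% | 1.8 h | 7.1 h | 6% | 68% | 70% |

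The pressers-only range covers the Mann–Whitney and t-tests. Repeat runs of the last row gave 66–68% for log-rank and 7–8% for pressers only, which is simulation error.

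**Sensitivity, 60 per arm.**
- Hazard ratio 0.67, median 12 h on ICNB (6% and 16% never pressing): 21% power among pressers against 54% for log-rank.
- Hazard ratio 0.67, median 24 h (25% and 40%): 9% against 44%.
- Blocks that differ only in the share who never need to press (10% and 30%), with the same timing otherwise: the difference among pressers is 0.0 h and the rejection rate 5%. The restricted mean difference is 6.3 h and log-rank power 58%.

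**The case against.** **Exclusion is not written down.** The article does not say that never-pressers are dropped. A patient known not to have pressed by 48 h has an observed state, and one could argue that the sentence on imputation does not concern that patient. Never-pressers also stay in the modified intention-to-treat set, which depends only on the primary outcome. This stands: exclusion is an inference from an undefined value together with no imputation, and the low power figures hold only under it.

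**The named rank test can work.** With never-pressers ranked at 48 h, Mann–Whitney power is 9, 4 and 2 points below log-rank in the three rows above. This also stands, but the article does not state that coding. Under it, a difference in means equals the restricted mean difference only if everyone is observed to 48 h, and it should then be labelled as such. As planned, it would be reported as a difference in time to first press.

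**Detail left to a fuller plan.** Data collection and registration mentions a prespecified statistical plan. But the article does not leave the method open: it assigns linear or logistic regression to the secondary outcomes. A plan that used Cox regression would depart from that text.

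**Two stronger readings are tempting and not supported.**
- A reader might infer that never-pressers will be common, because patients are told to press at NRS 4 or more and the pilot mean was 2.88 (SD 1.75). A normal approximation gives (4 − 2.88) / 1.75 = 0.64, or 74% below 4. But that pilot figure is a 72 h average of rest scores. One early peak, or pain on movement, is enough for a press, so the average says little about who never presses.
- A reader might infer that mobilization shares the bias against the better block. Patients not mobilized by 72 h would be the slowest, not the best, and are probably few. Excluding them would flatter the worse arm.

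**Conclusion.** The point holds for time to first press. The outcome is censored at 48 h by design, and the stated methods do not handle a censored time. Under the exclusion reading, half or more of the restricted mean difference is lost at a hazard ratio of 0.5, and power falls from 91%, 81% and 70% to about 40%, 14% and 6% as the never-press share on ICNB rises through 5%, 20% and 40%. Under the 48 h coding the rank test loses little, and the fault is confined to the linear model and the meaning of the reported difference.

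These sizes rest on assumed exponential times, hazard ratios and never-press rates. The documents do not show which reading will be used or how many patients will never press. No bias against the better block is claimed for mobilization. The primary outcome and the sample size are untouched. Severity: should-fix.

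**What to change.** In Statistical analysis, take time to first press out of the general rule for continuous data and state the following:

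- Kaplan–Meier curves and a log-rank test, censoring at PCIA stop (48 h) or at earlier removal of the pump.
- A Cox model adjusted for the same four covariates, with a hazard ratio and 95% confidence interval. An adjusted difference in restricted mean time to 48 h is an acceptable alternative.
- The number and proportion never pressing in each arm.
- The p-value carried into the existing Benjamini–Hochberg family.

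Time to independent mobilization may be handled the same way for consistency, censored at the end of its observation.

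The cost is a few sentences, agreed before unblinding. First-press time is already collected and the 48 h stop is fixed by design. The only possible addition is the actual stop time for a pump removed early, if the case report form does not already hold it. The sample size does not change.

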**Methods:**

This single-center, prospective, randomized, double-blinded trial will include 120 adult patients scheduled for VATS lung resection. Patients will be randomly assigned 1:1 to the ESPB group or ICNB group. Each patient will receive either an ESPB or ICNB at the end of the surgery, along with patients-controlled intravenous analgesia (PCIA) as part of a postoperative multimodal analgesia. The primary outcome is the average numeric rating scale (NRS) pain scores at rest over 72 h postoperatively (average of three 24-h time points: 24, 48, and 72 h). Secondary outcomes include NRS pain scores at rest and during activity at 24, 48, and 72 h postoperatively, Quality of Recovery 15 scores at 24, 48, and 72 h postoperatively, time to first press on the PCIA device, total opioid consumption within 72 h postoperatively, time to initiate independent bedside mobilization, length of postoperative hospital stay, and the incidence of chronic pain (defined as an NRS score ≥ 1) at 3 months post-surgery. Analyses will be performed in the modified intention-to-treat population.

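### One analysis set, defined by availability of the primary outcome and with no imputation, governs every comparison and discards data that exist

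*Protocol article*

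**What the plan says.** Under Statistical analysis, the set is a modified intention-to-treat population "comprising all randomized patients who undergo VATS lung resection and for whom primary outcome are available". The same section adds: "We do not plan to conduct missing data imputation or interim analysis". The abstract applies this set without limiting it to the primary outcome: "Analyses will be performed in the modified intention-to-treat population". No full intention-to-treat, safety or per-outcome set is named.

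Under Study outcomes, the primary outcome is the mean rest NRS, an "average of three 24-h time points: 24, 48, and 72 h". Entry to the analysis set therefore depends on data collected up to three days after randomization. The safety outcomes cover the same window: "Safety outcomes included postoperative adverse events and complications within 72 h".

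Under Sample size calculation: "Considering a 15% dropout rate, the study will enroll a total of 120 patients, with 60 in each group". Two features reduce losses. Randomization takes place when the specimen is removed (Randomization and blindness), and patients who go home before 72 h are assessed by telephone (Data collection and registration).

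**The concern.** The set is a complete-case set for the primary outcome, and the text extends it to everything else. That has three consequences.

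- **Secondary and safety data are lost for an unrelated reason.** A patient with known opioid use, hospital stay and 3-month pain status, but no pain average, drops out of all those comparisons. A patient with a serious early complication and no NRS scores would drop out of the adverse-event comparison.
- **Observed pain scores may be lost.** If all three scores are required, someone who gave scores at 24 and 48 h but could not be reached at 72 h contributes nothing to the primary analysis.
- **The primary comparison can be biased.** The article lists early discharge with telephone scoring as a limitation. Discharge timing plausibly follows recovery, and length of stay is itself an outcome, so missing 72 h scores need not be random or alike in the two arms.

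This is a rule that the article states, not a detail left to an unseen analysis plan.

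**Working it through.** **1. The plan's own figure.** Inputs from Sample size calculation and Statistical analysis: "assuming a standard deviation of 1.75, an 80% power, and a 0.05 level of significance", two-sided, 1:1 allocation, with the stated clinically important difference of 1 point read as the design difference. A two-group t-test (noncentral t) needs 50 per group (power 80.8%). Then 50/(1 − 0.15) = 58.8, so 59 per group and 118 in total, against 120 stated. The figure is reproduced. The 15% allowance is 0.15 × 120 = 18 patients, leaving 51 per group. Power is 81.5% with 51 per group and 87.4% with 60. Sample size is not the problem.

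**2. How many patients the rule could remove.** If all three scores are required and each is missing independently with probability p (an assumption), the share excluded is 1 − (1 − p)³:

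- p = 2%: 5.9%
- p = 5%: 14.3%
- p = 10%: 27.1%

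If one or two scores are enough, far fewer patients go, but they are then averaged over different days.

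**3. Where bias comes from.** In one arm, the mean of the full arm minus the mean of the observed patients is d × k, where d is the share missing and k is the gap between the missing and the observed mean. The bias of the complete-case difference is therefore −(d₁k₁ − d₂k₂).

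- 15% missing in both arms with equal k: 0.
- 10% against 20% missing, with missing patients 1 to 2 points worse: 0.1 to 0.2 points.

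**4. Size under an explicit mechanism.** Assumptions not in the document: correlation 0.7 between times, and probability of missing related to 24 h pain in one arm (odds ratio about 2.1 per SD) and unrelated in the other.

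- The correlation of the 24 h score with the three-score average is √[(1 + 2 × 0.7)/3] = 0.894. One SD of 24 h pain thus corresponds to 1.75 × 0.894 = 1.565 points of the average.
- At 15% missing, missing patients lie about 0.69 SD above observed ones on 24 h pain: k = 0.69 × 1.565 ≈ 1.08, and the bias is 0.15 × 1.08 ≈ 0.16.
- At 5% missing, the gap is about 0.72 SD: k ≈ 1.13, and the bias is 0.05 × 1.13 ≈ 0.06.

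Simulated trials (60 per arm, true difference −1.00, 14–15% missing the 72 h score, half of those also missing 48 h) gave complete-case estimates of −0.81 or −1.19 depending on which arm had the pain-related loss. A likelihood analysis of all available scores gave −1.00 both ways. With the same mechanism in both arms and 9–12% missing, the complete-case estimate was −0.97.

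**5. Precision at 15% missing at random.** In simulation the standard error was about 0.34 for complete cases and 0.32 using all scores. As a check, 1.75 × √(2/51) = 0.347 and 1.75 × √(2/60) = 0.320.

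**6. What such a bias would do.** With 51 per group, a bias of 0.1 or 0.2 points raises the 5% type I error to 5.9% or 8.8%. If it runs against a true 1-point effect, it lowers power to 73% or 63%.

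**The case against.** The strongest reply is that the rule is openly prespecified and the harm is conjectural. Much of that stands.

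- A reader might infer that one missing score always removes a patient. The text does not say so. It requires the primary outcome to be available and leaves open whether an average of one or two scores counts. The simulations in the working take the stricter reading.
- A reader might infer that 18 of 120 patients will leave every analysis. The 15% is an allowance in the sample size, not a forecast, and telephone follow-up may keep losses on a 72 h endpoint well below it.
- A reader might infer that patients are selected on their pain, or that late randomization is undone. Selection is on availability, not on value. Randomizing at specimen removal still prevents exclusions for cancelled resections, so the surgery criterion is nearly harmless.
- The larger bias needs an asymmetry between arms that blinding of patients and assessors makes less likely. Even 0.18 points is about half a standard error and under one-fifth of the 1-point difference.
- The simulated missingness depends only on observed 24 h pain, so the likelihood analysis is unbiased by construction. Loss driven by unobserved later pain or complications is not covered.

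None of this justifies removing patients from secondary and safety comparisons because a different outcome is missing.

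**Conclusion.** The concern holds in a limited form. What is certain from the text is that a single set, conditional on availability of the primary outcome and without imputation, applies to the analyses in general. Followed literally, it drops patients whose secondary and safety data exist. Loss of observed rest scores from the primary analysis depends on a partial-score rule that the article does not give.

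The document does not show that the primary comparison is biased, and it does not let anyone say by how much. Under the assumptions stated, the range runs from near zero (same mechanism in both arms) through 0.05–0.06 points (5% missing, pain-related in one arm only) to 0.16–0.19 points (15% missing), in either direction, with a modest loss of precision. This should be corrected, but it is not an established flaw that invalidates the trial.

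**What to change.** - **Population:** analyse all randomized patients in their assigned arm.
- **Primary outcome:** fit a linear mixed model to all available rest NRS scores at 24, 48 and 72 h, with the treatment difference averaged over the three times as the primary contrast. With complete data this targets the same mean difference as the current endpoint, and the question of partial averages no longer arises in the primary analysis.
- **Secondary outcomes:** analyse each in all randomized patients who have that outcome.
- **Adverse events:** report in all patients who received a block.
- **Sensitivity analyses:** keep the complete-case average, stating how many scores it requires, and add an analysis under missing-not-at-random assumptions.

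The cost is revised wording, slightly more programming, and reliance on missing at random for the primary model, which the added sensitivity analysis is meant to probe. No new data are needed and the sample size stays at 120. The change should be made before allocation is unmasked.
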